### Step 5: Program Implementation Plan

Patients undergoing major abdominal, general surgical, or gynecological procedures were identified as new program users. No new professionals were identified as program users as the introduction and implementation of the program would remain in the perioperative phase also for the extended patient group. The 7 hospitals that participated in the earlier performed “ikherstel” study wished to continue the use of the “ikherstel” intervention including broadening the usage of “ikherstel” intervention at the general surgery department of their hospital. Many other general hospitals in different regions in the Netherlands signed the letter of intent to participate in this multicenter study. After a kick-off meeting at the research institute, one meeting with surgeons or gynecologists (depending on the department) and one meeting with nurses per hospital was held to discuss the content and logistics of the study and its implementation. Finally, 10 general surgery practices and 8 gynecology practices (all teaching hospitals) were positive about the further development of “ikherstel” intervention and willing to implement the intervention. They will participate in the evaluation of this intervention through implementation of the eHealth intervention as a supplement to the standard perioperative care given at their hospital.

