#### Sample Size Calculation

To detect a hazard ratio of 1.4 for RNA (corresponding to a decrease in median time to RNA from 10 weeks to 7.14 weeks as a result of the intervention) with 80% power while testing using a 2-sided log-rank test at a significance level of 5%, a total of 318 events need to be observed. The total sample size is set at 354 (177 per arm) to account for an anticipated proportion of 2.5% of patients not returning to daily activities within the 12 month follow-up period and a dropout rate of 10%.

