#### Recruitment, Inclusion, Allocation, and Blinding of Patients

Patients will be recruited for study participation when they are on the waiting list in one of the participating hospitals and will receive a study information letter on behalf of their doctor. Contact will be made by phone to check their willingness to participate and to access eligibility. Eligible patients willing to participate will be included. After the patient completes the baseline questionnaire T(0) within 2 week before surgery and has signed informed consent, randomization will be executed by an (independent) research assistant. A computer-generated randomization in a 1:1 ratio will be performed on individual level stratified regarding hospital, sex, and surgical procedure using permuted blocks of size 2. Patients will be blinded to the intervention, as they do not know which program is developed as a nonintervention or intervention care program. The researchers involved in the analyses will be blinded to the allocation throughout the analyses. Health care professionals cannot be blinded to the intervention because it is highly likely that they will be notified of the allocation either by the patient or the patients’ medical file.

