#### Data Analyses Plan

All analyses will be performed in IBM SPSS. Baseline characteristics will be summarized using descriptive statistics and compared between the intervention and control group using *t* tests by normal distributions of variables and Mann-Whitney *U* tests, chi-square tests, or Fisher exact tests by non-normal distributions of variables. Our primary outcome, time until full RNA, will be analyzed by both crude and adjusted survival analyses where hospital, surgical procedure, and sex will be taken into account as covariates in the adjusted analyses due to stratification. To describe the distribution of the duration until RNA in both groups, the Kaplan Meier method will be used. The Cox proportional hazard model will be applied to calculate hazard ratios. Adjustments will be made if there are clinically relevant differences between the intervention and the control group in the baseline characteristics or if other potential confounding factors are observed. For the longitudinal secondary outcomes, mixed models and multilevel logistic regression models will be performed. For the cross-sectional secondary outcomes, *t* tests, Mann-Whitney *U* tests, chi-square tests, or Fisher exact tests will be used to compare differences. Intention-to-treat analyses will be compared with per-protocol analyses to identify whether there are differences if patients used the intervention as intended. Subgroup analyses will be performed regarding the surgical procedure (colectomy and hysterectomy) and indication (benign or malignant disease). A post hoc analysis will be carried out on patients without major complications.

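### The tests named for cross-sectional secondary outcomes ignore the randomisation strata; they are conservative to the extent that hospital, sex and procedure are prognostic

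*Protocol article*

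**What the plan says.** Three statements in the protocol article bear on this.

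- **Allocation** (Recruitment, Inclusion, Allocation, and Blinding of Patients): patients are allocated individually, in equal numbers to the two arms. The scheme is "stratified regarding hospital, sex, and surgical procedure using permuted blocks of size 2".
- **Primary outcome** (Data Analyses Plan): crude and adjusted survival analyses are both planned. In the adjusted ones, "hospital, surgical procedure, and sex will be taken into account as covariates in the adjusted analyses due to stratification".
- **Cross-sectional secondary outcomes** (same section): the article lists the t test and the Mann-Whitney U test and ends the list with "chi-square tests, or Fisher exact tests will be used to compare differences". No stratification factor is mentioned.

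A further sentence in the Data Analyses Plan allows covariates on a data-dependent basis: "Adjustments will be made if there are clinically relevant differences between the intervention and the control group in the baseline characteristics", or if other confounding is seen. It stands after the Cox model and before the secondary outcomes.

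**The concern.** Stratified allocation in small blocks removes most of the between-stratum differences from the contrast between arms. A plain two-group test does not know this. Its standard error still counts differences between colectomy and hysterectomy, between hospitals and between the sexes as random noise. If those differences are real, the reported standard error exceeds the true variability of the estimate. Intervals are then too wide, the test rejects less often than 5% under no effect, and some true differences are missed.

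The plan accepts this reasoning for the primary outcome and then names tests that cannot follow it for other outcomes. The tests are stated, so this is not detail left to a statistical analysis plan. The imbalance-triggered sentence does not repair it: stratification makes imbalance on these three factors unlikely, so the trigger would rarely bring them in, and the named tests could not carry them anyway.

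The article gives reasons to expect some prognostic value. Malignancy is excluded for hysterectomy but not for colectomy (Eligibility Criteria). The literature review links convalescence to pain, complications, fear of recurrence and incision size. Subgroup analyses by procedure and indication are planned.

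**Working it through.** **The plan's own figure.** The article gives no power or standard error for these outcomes. Its sample-size figures concern the log-rank test on the primary outcome. For a hazard ratio of 1.4, two-sided 5% and 80% power, the Schoenfeld formula gives 4 x (1.960 + 0.842)^2 / (ln 1.4)^2 = 277.3, so 278 events, not the stated 318. The stated count matches 85% power. That is a separate matter and nothing below depends on it.

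**Inputs from the article**
- 354 randomised less 10% dropout: 354 x 0.90 = 318.6, taken as 318 completers. That this equals the stated event count is a coincidence of use here.
- 1:1 allocation in permuted blocks of 2.
- Ten surgical and eight gynecological practices: 10 x 2 sexes + 8 = 28 strata. This assumes that hysterectomy patients are all female and that open and laparoscopic approaches are not separate strata.

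**Assumed inputs**
- R2, the share of outcome variance explained by the strata: not in the documents, so varied from 0 to 0.40.
- A true difference of 0.315 total SD, chosen to give about 80% power at R2 = 0.

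**Formula.** With total SD 1, the t test reports a standard error of about 2/sqrt(318) = 0.112. Under near-perfect stratum balance the true SD of the estimate is about 0.112 x sqrt(1 - R2). The reported value is therefore too large by f = 1/sqrt(1 - R2), and the real two-sided error is 2 x [1 - Phi(1.96 f)].
- R2 = 0.10: f = 1.054; 1.96 f = 2.066; error 3.9%.
- R2 = 0.20: f = 1.118; 1.96 f = 2.191; error 2.8%.
- R2 = 0.30: f = 1.195; 1.96 f = 2.343; error 1.9%.

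**Simulation.** 6,000 trials per setting, continuous outcome, pooled t test against a linear model with stratum effects.

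| R2 | Reported SE / true SD (t test) | Type I error, t test vs adjusted | Power, t test vs adjusted | Points lost |
|---|---|---|---|---|
| 0 | 1.00-1.01 | 4.8% vs 5.0% | 79.9% vs 79.6% | none |
| 0.05 | 1.01-1.03 | 4.9% vs 5.5% | 81.0% vs 82.0% | 1.0 |
| 0.10 | 1.05-1.07 | 3.6% vs 4.6% | 81.5% vs 83.4% | 1.9 |
| 0.20 | 1.10-1.12 | 3.0% vs 4.7% | 82.4% vs 87.8% | 5.4 |
| 0.30 | 1.19-1.20 | 2.0% vs 5.0% | 84.0% vs 91.3% | 7.3 |
| 0.40 | 1.26 | 1.5% vs 5.3% | 85.8% vs 95.0% | 9.2 |

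The simulation error is about sqrt(0.05 x 0.95/6000) = 0.3 points for a 5% rate and sqrt(0.8 x 0.2/6000) = 0.5 points for 80% power, so formula and simulation agree closely. The t test's own power rises with R2 because the effect is fixed in total SDs; the gap between the two analyses is what matters.

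**What these R2 values mean.** If procedure alone were prognostic and the two procedures equally common, a gap of d within-procedure SDs gives R2 = d^2/(4 + d^2), so d = 2 x sqrt(R2/(1 - R2)). R2 of 0.10, 0.20 and 0.30 then needs a gap of 0.67, 1.00 and 1.31 SD. Hospital and sex effects would lower the gap needed.

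**Binary outcome, illustration.** Assume an equal split and event rates of 50% and 70% by procedure. The between-procedure variance is 0.10^2 = 0.01 and the total variance 0.6 x 0.4 = 0.24, so R2 = 0.042 and f = 1.02: a standard error about 2% too large.

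**The case against.** The strongest reply is that the effect is conditional and may be small. Nothing in the documents fixes R2 for any secondary outcome. At 0.05 to 0.10 the loss is 1 to 2 points of power, and reaching 0.20 through procedure alone takes a gap of a full SD. That stands, and it is why the size is given as a range from zero.

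Other limits also stand:
- Only a t test on a continuous outcome was simulated. The Mann-Whitney, chi-square and Fisher tests were not, and the binary illustration suggests a smaller loss there.
- Multimedia Appendix 5, which lists outcomes by measurement moment, is not shown. It cannot be said which outcomes are cross-sectional, or whether patient satisfaction is one of them.
- The trial is powered for the primary outcome only, so no promised power is broken.

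Stronger readings are tempting but unsupported. A reader might infer that every single-time outcome carries a standard error 10-20% too large; that needs an R2 of about 0.20-0.30, which the documents do not give. A reader might infer that secondary results rest on a wholly different basis from the primary; but the primary outcome is also analysed crude, and plain tests parallel that. A reader might add the gain from adjusting for a baseline value; but no cross-sectional outcome is shown to have one, longitudinal outcomes go to mixed or multilevel models, and that gain is a different issue from the strata.

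What the reply does not remove is that the design and the named tests do not match, and that adjustment costs practically nothing when the strata carry no information (79.6% against 79.9% power).

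**Conclusion.** The point holds as a conditional loss of efficiency. The named tests ignore strata that the plan itself treats as calling for adjustment of the primary outcome. To the extent that those strata are prognostic, the tests are conservative. For a continuous outcome the cost runs from nothing at R2 = 0 to about 5 points of power at 0.20 and 7 at 0.30, with type I error falling to about 3.0% and 2.0%. These sizes rest on the assumed R2, 318 completers, 28 strata and an effect of 0.315 SD. The direction is well supported; the size is not known.

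It creates no false positives, does not invalidate any result, and leaves the primary outcome alone. It is worth correcting because the correction is nearly free, not because the harm is large.

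**What to change.** Replace the sentence on cross-sectional secondary outcomes with wording such as: the main comparison will be a linear or logistic regression on arm, adjusted for hospital, sex and surgical procedure, with hospital as a random effect or pooled where numbers are sparse; effects will be reported with 95% confidence intervals; the unadjusted tests will be given as the crude analysis. Where a rank or table test is preferred, use its stratified form (van Elteren, or Cochran-Mantel-Haenszel), with an effect estimate and interval alongside.

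The cost is a sentence of wording. The three factors are already recorded for randomisation, so no new data or patients are needed, and covariate-adjusted models are already planned for other outcomes. There are small downsides. Logistic adjustment yields a conditional odds ratio, which should be labelled as such. Sparse binary outcomes may support adjustment for procedure and sex only, so part of the stratification would stay unaccounted for there. The choice should be fixed before the allocation is known to the analysts.

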#### Process Evaluation

In the earlier performed “ikherstel” study, 210 patients were included, of which 110 patients were allocated to the intervention group. The implementation score of the intervention was 80%. All patients were given access to the “ikherstel” intervention and 86.4% made a convalescence plan. Reasons for not making or not adhering to the convalescence plan include patients (1) preferred to resume activities when they felt ready for it, (2) found the convalescence plan too optimistic or too conservative, (3) felt pushed by the convalescence plan, and (4) felt that the plan did not apply to their personal situation.

The eHealth intervention was perceived effective by 74% of patients, and 76% of involved gynecologists were satisfied with the Web portal. In total, 95% of the health care professionals would offer the intervention to their patients in the future, and 85.3% of patients would recommend the “ikherstel” eHealth program to a friend.

Required access to internet, the inflexibility of the eHealth intervention in case of complications for patients, and an increased time investment for gynecologists were rated as possible future usage barriers. Suggestions for improvement included an extra section with experiences of other women. All results of the process evaluation are published in detail elsewhere [26].

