#### Review of the Literature

The systematic review included 27 studies that focused on replacing or complementing perioperative usual care with some form of care via information and communication technology (ICT) such as telemonitoring, telerehabilitation, teleconsultation, or an educational or supportive website in various types of surgery. Of these studies, 92% reported at least an equal or positive effect of the eHealth intervention compared with usual care on patient-related outcomes. The results show that eHealth or other forms of ICT and telehealth improve clinical outcomes, knowledge, and satisfaction of patients undergoing various forms of surgery. Furthermore, eHealth improves RTW and daily functioning after surgery. Positive influencing factors on these patient-related outcomes were (1) easy access to the intervention, (2) expectation management, and (3) a combined symptom monitoring by blended care [27].

The literature search in the IM protocol article of Vonk Noordegraaf et al identified that pain and discomfort, feelings of fear, and infections were delaying factors for RTW [19]. In addition, literature showed that the substantial variation in convalescence recommendations given by health care professionals were also of influence on the total duration of sickness absence [9,30]. In the broadened search, a wide variety in convalescence duration after minor general surgical procedures (eg, cholecystectomy and hernia inguinal repairs) was observed [31,32]. For major abdominal procedures, limited research was available to analyze the time of full recovery including RNA (and RTW) [33-36]. However, literature does show that the total duration of convalescence was longer than expected despite the implementation of minimal invasive techniques and ERAS programs applied by major abdominal procedures [1,37,38]. Duration of convalescence depends on pain, complications, or fear of recurrence (in case of cancer of hernia inguinal repairs) [39-41]. Preoperative expectations of convalescence, size of the incision, and fatigue were important contributory factors to explain actual convalescence [39-42]. Furthermore, patients who were physically active after colorectal surgery were more likely to recover faster [43].

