#### Outcome Measures

Our primary outcome measure is RNA. The Patient-Reported Outcomes Measurement Information System physical functioning item bank version 1.2 will be used to measure limitations in daily activities. A list of 29 most relevant selected activities will be presented to participants before surgery with the goal to select 8 activities, which are most relevant for them in their daily life. They will be asked in the following questionnaires after surgery if they can already perform one of these 8 activities. RNA is defined as the time in calendar days from the day of surgery until a participant has resumed all activities [57,58].

Secondary outcomes are social participation, self-rated health, duration until RTW, physical activity, length of recovery, pain intensity, and patient satisfaction [59-63]. Costs will be measured from a societal and health care perspective and consist of costs of the intervention, health care utilization costs, and costs associated with lost productivity [64,65]. Sociodemographic data and questions regarding expectations about the length of recovery and the amount of anxiety will be assessed at the baseline measurement. Complications will be assessed by reviewing the surgical reports and postoperative notes and scored by using the Clavien-Dindo classification [66]. The outcome measures will be obtained by using questionnaires administered at baseline (approximately 1-2 week preoperative) and at 2, 4, and 6 weeks and 3, 6, 9, and 12 months after surgery. For a total overview of all outcomes per measurement moment of this study, see Multimedia Appendix 5.

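### The per-protocol and complication-free analyses select on events after randomisation, so neither supports a treatment-effect conclusion; the intention-to-treat result is unaffected

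*Protocol article*

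**What the plan says.** All references are to the protocol article.

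- **Timing of randomisation** (Recruitment, Inclusion, Allocation, and Blinding of Patients): "After the patient completes the baseline questionnaire T(0) within 2 week before surgery and has signed informed consent, randomization will be executed". Allocation is therefore fixed before surgery.
- **Per-protocol analysis** (Data Analyses Plan): "Intention-to-treat analyses will be compared with per-protocol analyses to identify whether there are differences if patients used the intervention as intended".
- **Restricted analysis** (same section): "A post hoc analysis will be carried out on patients without major complications".
- **Source of the complication data** (Outcome Measures): "Complications will be assessed by reviewing the surgical reports and postoperative notes and scored by using the Clavien-Dindo classification". On the staff who write those notes, the blinding section says: "Health care professionals cannot be blinded to the intervention".
- **Uptake in the earlier study** (Results, Step 1, Process Evaluation): "86.4% made a convalescence plan". Among the reasons for not making or not following the plan was that patients "preferred to resume activities when they felt ready for it". Others found the plan too optimistic or too cautious. The same section names the programme's inflexibility when complications occur as a possible barrier to use.
- **Determinants of recovery time** (Results, Step 1, Review of the Literature): "Duration of convalescence depends on pain, complications, or fear of recurrence".

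Neither restricted analysis is called primary. The Data Analyses Plan allows adjustment for baseline differences and other observed confounders. It gives no method aimed at the selection and places no limit on how the two results may be read.

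**The concern.** Randomisation makes the arms comparable as allocated. It does not make subsets comparable when membership is decided afterwards by something related to outcome. Both planned subsets are of that kind.

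For the per-protocol analysis the weak point is the stated purpose. A gap between the ITT and per-protocol results is to show what happens when the programme is used properly. The gap mixes that effect with the prognosis of those who choose to use the programme or are well enough to do so. A more detailed definition of proper use would not separate the two.

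For the complication-free analysis, the programme offers recovery monitoring, electronic consultations and encouragement to mobilise early. It could change how often major complications occur or are recorded. If so, the patients left in each arm differ in vulnerability.

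At stake is a secondary claim that the programme works if used, or works in uncomplicated patients, without randomised support.

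**Working it through.** The plan gives no figure for either analysis, so there is nothing to reproduce. The event count in Sample Size Calculation concerns the primary test and does not enter here.

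**Inputs from the article:** 354 patients, 1:1; median time to resumption of normal activities (RNA) 10 weeks without the intervention; 12-month follow-up; 10% dropout; non-use 100% − 86.4% = 13.6%, taking a plan made as use.

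**Assumed inputs:** exponential recovery times; relative prognosis of non-users; a 30% non-use variant; complication rates; the effect of allocation on complications; exclusion of non-users from the intervention arm only.

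**Simulation:** 4,000 trials per setting, two-sided log-rank test at 1.96, Cox hazard ratio (HR). An HR above 1 means faster recovery with the intervention.

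**1. Per-protocol set, no true effect.** Let q be the non-use share and h the recovery hazard of non-users relative to users. The intervention arm keeps users only (hazard 1). Controls keep both types. At the start of follow-up the ratio is

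HR₀ = 1 / (1 − q + q·h).

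For q = 0.136 and h = 0.6: 1 / (0.864 + 0.0816) = 1.06. The ratio then grows, because slow recoverers accumulate among controls still at risk. The Cox HR over a year is therefore larger.

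| q | h | HR₀ by formula | Simulated HR | Type I error |
|---|---|---|---|---|
| 13.6% | 1.0 | 1.00 | 1.00 | 4.8% |
| 13.6% | 0.8 | 1.03 | 1.03 | 6.0% |
| 13.6% | 0.6 | 1.06 | 1.08 | 10.2% |
| 13.6% | 0.4 | 1.09 | 1.16 | 24.4% |
| 30% | 0.8 | 1.06 | 1.07 | 8.8% |
| 30% | 0.6 | 1.14 | 1.18 | 27.5% |
| 30% | 0.4 | 1.22 | 1.35 | 69.1% |

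**2. Per-protocol set, opposite direction.** Let non-users recover faster (h = 1.25, 1.5, 2) and let the true HR in users be 1.4. With 13.6% non-use the per-protocol HR is 1.37, 1.33, 1.30. With 30% non-use it is 1.31, 1.26, 1.18. With 30% non-use and equal prognosis it is 1.40, so the distortion comes from prognosis and not from removing patients as such.

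**3. Complication-free set, no true effect on recovery.** Let p be the control complication rate (10% or 20%), r the risk ratio by arm, and h the recovery hazard of vulnerable patients (0.5 or 0.3), who stay slow whether or not the complication is prevented or recorded.

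- r = 1: simulated HR about 1.00, type I error 4.8% to 5.6%. No bias.
- r = 0.5: all vulnerable controls are dropped, but half of the vulnerable intervention patients remain. With p = 0.2 and h = 0.3 the starting ratio is (0.8 + 0.1 × 0.3) / 0.9 = 0.92, and the simulated HR is 0.86. Across settings the HR is 0.96 to 0.86, with rejection in 7% to 26% of trials.
- r = 1.5: the reverse. With p = 0.2 and h = 0.3 the starting ratio is 0.8 / (0.7 + 0.1 × 0.3) = 1.10, and the simulated HR is 1.19. Across settings the HR is 1.05 to 1.19, with rejection in 7% to 26% of trials.

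**The case against.** **The analyses are supplementary.** ITT is kept, and nothing says that conclusions will rest on the subsets. This stands. A reader might infer that the trial's main result is compromised, and the article does not support that.

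**The per-protocol set is not defined here.** This stands, and a condensed article may leave the definition to the full protocol. A reader might infer that users will be compared with all controls. The article does not say so. Its blinding text, under which patients do not know which programme is the intervention, hints that controls also receive something whose use could be judged, although Study Design speaks of usual care. The figures above therefore illustrate one plausible construction. Selecting on use in both arms would not restore the randomised comparison either, because using two different programmes can select different patients.

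**The complication scenario is assumed.** The listed programme objectives do not include preventing major complications, and with equal risks there is no bias. This stands. A reader might infer that the complication-free result must be wrong. It is biased only if allocation changes the occurrence or recording of major complications.

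**The larger biases need strong assumptions.** This is correct. With 13.6% non-use and h of 0.8 to 0.6, the HR is 1.03 to 1.08 and type I error 6% to 10%. The earlier study's reasons for non-adherence do not fix a direction.

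**Covariate adjustment is allowed, and the post hoc label already signals caution.** Adjustment can reduce selection through measured baseline variables, but not through how recovery itself goes. The label covers only one of the two analyses and sits oddly on an analysis planned in advance. That is a wording point and no more.

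**Conclusion.** The point holds in limited form. Both restricted analyses condition on events after randomisation that the article links to recovery, so neither is a randomised comparison. The inference attached to the ITT versus per-protocol contrast is not secured by the design. The primary ITT result is untouched.

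The possible size runs from nothing, if non-users have the same prognosis as users or complications are equal by arm, to the simulated ranges: a null per-protocol HR of about 1.03 to 1.16 at 13.6% non-use, or a null complication-free HR of about 0.86 to 1.19. These rest on the assumed prognosis of non-users and of vulnerable patients, on removal from one arm only, and on complication risk ratios of 0.5 and 1.5. They show what can happen and do not predict this trial's bias. This is a change worth making to the interpretation of secondary analyses and is not a flaw in the main test.

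**What to change.** 1. State that treatment conclusions rest on ITT only. Describe the per-protocol and complication-free analyses as exploratory and non-randomised, supporting no treatment-effect conclusion. Drop the post hoc label for an analysis planned in advance.
2. Compare major complications by arm in all randomised patients. The Clavien-Dindo scores are already collected.
3. If the effect in users is wanted, add a complier-average estimate with randomisation as instrument, without substituting it for another analysis. An example is the proportion with full RNA at 6 weeks and 3 months, with use defined as any access or a plan made. The estimate is the ITT difference in proportions divided by the difference in use between arms. This requires that usage is recorded and that controls cannot access the programme. The article states neither, so both are assumptions to confirm.

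**Cost:** items 1 and 2 need wording and one table. Item 3 needs one more model and gives a wider interval: at 86.4% use, about 1 / 0.864 = 1.16 times the width of the ITT interval. Its estimand, a proportion at a fixed time, differs from the Cox HR. It also relies on the exclusion restriction, which is harder to defend if use means a plan made, since patients without a plan may still use other tools.
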